### Study objectives and hypotheses

The objectives and hypotheses of the current study are:To evaluate the effect of FBSFT compared to TAU for severe childhood and adolescent obesity in a common health care setting. The primary outcome is weight status, assessed as BMI, BMI standard deviation scores (SDSs) and percentages above the IOTF cut-off for overweight (%IOTF-25) [41]. Secondary outcomes are other weight-related anthropometric measurements (waist circumference (WC) and Waist-to-height ratio (WHtR) and corresponding SDSs), body composition (BIA, DXA), blood test, blood pressure, eating habits, sleep, physical activity as well as psychological well-being and parenting style.○ We hypothesized that FBSFT will be superior to TAU in improving these parameters both during the intensive treatment period and during the follow-up period.
To identify predictors of treatment success and treatment drop out with a focus on family variables, socioeconomic status, social network and mental health.○ We expect children from families in which both parents participate in treatment to demonstrate better weight loss outcome and have lower dropout rate.○ We expect children of parents living together to demonstrate better treatment effects and have lower dropout rate.○ We expect that parental (self-reported) weight status will influence treatment effects and dropout rate; higher BMI category will predict poorer treatment effects and higher dropout rate.○ We expect that lower socio-economic status and limited social network will predict poorer treatment effects and higher dropout rate.○ We expect poorer treatment effect and higher dropout rate among participants with psychological comorbidities.
To evaluate experienced barriers to treatment, and how these factors influence children’s and parents treatment response. Barriers to treatment are classified into four groups: competing activities/life stressors, relevance of treatment, treatment issues (logistics) and critical events.○ We expect lower degree of competing activities/life stressors to predict better treatment response and lower dropout rate.○ We expect higher degree of experienced treatment relevance to predict better treatment response and lower dropout rate.○ We expect lower degree of treatment issues and lower number of critical events to predict better treatment response and lower dropout rate.

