### Inclusion criteria

The sample will consist of 120 children and adolescents (aged 6–18 years) referred to the OOC by their general practitioner. Criteria for admission to the clinic is an International Obesity Task Force (IOTF) BMI ≥ 35, or ≥ 30 [41] with obesity related co-morbidity. The child/adolescent participates in the treatment together with her/his family, such that both the child and a least one of the parents agree to actively participate in the treatment.

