### Anthropometrical measures

Trained assessors at the OOC will measure height and weight for calculation of BMI (kg/m2), WC and body composition (measured with bio impedance (BIA), InBody 720). BMI will be converted to SDS using the extended IOTF [41, 44] BMI references. The percentage of the IOTF 25 threshold (%IOTF-25) is calculated as 100*(BMI/IOTF 25), where BMI is the child’s weight divided by height squared (kg/m^2^), and IOTF 25 is the BMI that corresponds to the IOTF threshold for overweight for the child’s age and sex. Dual-energy X-ray absorptiometry (DXA)-scans for determining the distribution of fat and muscle tissue will be conducted at the Department of Rheumatology at Haukeland University Hospital.

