## Planned data analysis

A two-way MANOVA with one repeated-measure factor (Time: pre-intervention/post-intervention), and one between-group factor (Treatment Group: FBSFT vs. TAU) will be conducted to assess the impact of treatment on primary and secondary outcomes.

A one way within-subjects MANOVA will be used to analyze the effect of time (pre-treatment, post-treatment, 12-, 18-, 24 months post treatment) on primary and secondary outcomes.

In order to identify factors associated with treatment success and treatment drop out, multiple regression analyses will be conducted. The dependent variables are %IOTF-25 and drop-out status (yes/no). The predictors are: both parents participating in treatment, parental marital status, self-reported parental weight, socio-economic status and social network, psychological comorbidities.

In order to identify barriers to treatment and how these barriers influence children’s and parents’ treatment response, multiple regression analyses will be conducted. The dependent variable is %IOTF-25. The predictors are: competing activities/life stressors, relevance of treatment, treatment issues (logistics) and critical events.

Intention-to-treat analyses will be conducted and effect sizes calculated for treatment effects.

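### The uncontrolled 24-month time analysis tests raw BMI and raw waist circumference in growing children, so its time effect mixes growth with treatment

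*Protocol article*

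**What the plan says.** Study objectives and hypotheses gives three measures of the primary outcome and ranks none of them first: "The primary outcome is weight status, assessed as BMI, BMI standard deviation scores (SDSs) and percentages above the IOTF cut-off for overweight". Raw waist circumference is among the secondary outcomes, together with waist-to-height ratio and SDS versions of the waist measures.

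Planned data analysis has two MANOVAs. The first has a treatment-group factor and two time levels, before and after the intervention. The second has no group factor: "A one way within-subjects MANOVA will be used to analyze the effect of time". Its full scope is the "effect of time (pre-treatment, post-treatment, 12-, 18-, 24 months post treatment) on primary and secondary outcomes", so raw BMI and raw waist are included. The text neither excludes them from this analysis nor adjusts them for age or expected growth.

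Anthropometrical measures defines %IOTF-25 as 100 × BMI / IOTF 25, where "IOTF 25 is the BMI that corresponds to the IOTF threshold for overweight for the child’s age and sex". Inclusion criteria sets the population: "The sample will consist of 120 children and adolescents (aged 6–18 years) referred to the OOC by their general practitioner".

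**The concern.** A within-subjects analysis compares each child with the same child up to two years earlier. In a sample that includes 6-year-olds and teenagers, raw BMI and waist can change because the child has grown. Without a comparison arm, the one-way model cannot separate that change from treatment.

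This analysis also carries the long-term message. Under Trial design, arm B starts FBSFT after one year, so no TAU-only group remains beyond that point. Of the MANOVAs specified, only the one-way time analysis reaches 18 and 24 months.

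A group whose relative weight is stable or modestly better could therefore show a significant rise in one primary measure while the other two are flat or falling. With no ranking among the three, the long-term result is open to selective reading. If the measures enter one joint MANOVA, which the text does not settle, the multivariate time test could be significant through growth alone.

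**Working it through.** **The plan's own figures.** Sample size gives 164, 28 and 12 for f = 0.10, 0.25 and 0.40 (2 groups, 3 time points, correlation 0.5, alpha 0.05, power 0.80). With noncentrality f² × N × 3 / (1 − 0.5) and degrees of freedom 2 and 2(N − 2), these Ns reproduce exactly, with power 0.805, 0.812 and 0.810. They concern the group × time test and say nothing about growth drift. The plan gives no figure for the one-way time analysis.

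**Inputs from the protocol.** The %IOTF-25 formula; a threshold specific to age and sex; ages 6–18; a last visit at 24 months (Outcome measures); 60 families per arm; correlation 0.5; alpha 0.05.

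**Assumed inputs.** The threshold rises with age, by g = 0.25 to 1.0 kg/m² per year; %IOTF-25 is 140; the cross-sectional BMI SD is 5; the starting threshold, where needed, is 18 to 22 kg/m².

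**Step 1: drift at constant relative weight.** Rearranging the protocol's formula, BMI = (%IOTF-25 / 100) × IOTF 25. With %IOTF-25 fixed at 140, the 24-month change in BMI is 1.40 × 2g:
- g = 0.25: 0.7 kg/m²
- g = 0.5: 1.4 kg/m²
- g = 0.75: 2.1 kg/m²
- g = 1.0: 2.8 kg/m²

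At 120% the range is 0.6–2.4 and at 160% it is 0.8–3.2.

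**Step 2: chance of a significant upward time effect when relative weight has not changed.** I use a two-sided 5% paired t-test of baseline against 24 months as a simple stand-in for the five-point model. The SD of change is SD × √(2(1 − correlation)), which is 5 at correlation 0.5 and 3.16 at 0.8. With 60 children, SD 5 and correlation 0.5, the noncentrality for a drift of 1.4 is 1.4 / (5/√60) = 2.17. Without drift, the chance of an upward rejection would be 2.5%.

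| Children, SD, correlation | drift 0.7 | 1.4 | 2.1 | 2.8 |
|---|---|---|---|---|
| 60, 5, 0.5 | 19% | 57% | 89% | 99% |
| 60, 5, 0.8 (assumed) | 39% | 92% | >99% | >99% |
| 120, 5, 0.5 | 33% | 86% | >99% | >99% |

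The article does not say whether one arm or both enter this analysis, so both 60 and 120 are shown. Dropout would lower the percentages.

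**Step 3: modest improvement.** BMI stays flat only if %IOTF-25 falls by 140 − 140 × b/(b + 2g) points, where b is the starting threshold. For b = 18 to 22 this is 3.1–3.8 points at g = 0.25 and 11.7–14.0 points at g = 1.0. For example, with b = 18 and g = 0.5, a 5-point fall in %IOTF-25 gives 1.35 × 19 − 1.40 × 18 = 25.65 − 25.20 = +0.45 kg/m². Relative weight improves while BMI rises.

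**Step 4: the randomised comparison.** In 4,000 simulated trials with 60 per arm, a drift of 1.4 common to both arms, SD 5 and correlation 0.8, the within-group time test rejected in 92% and the group × time test in 5%. The problem belongs to the uncontrolled analysis.

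**The case against.** The strongest reply is that the protection is already in the plan. BMI SDS and %IOTF-25 are co-listed as primary and referenced to age and sex, waist SDS and waist-to-height ratio are also listed, and the regressions use %IOTF-25 as their only weight outcome. A BMI rise beside flat standardised measures would be visible in the same analysis. The plan also assigns the assessment of treatment impact to the two-way MANOVA and describes the one-way model as an analysis of time. All of this is correct and limits the weight of the point. It does not remove it, because a growth-confounded primary measure is still tested, unranked, at time points no controlled analysis reaches.

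A second reply is that an uncontrolled pre–post analysis of a referred, severely obese sample is open to regression to the mean and maturation on every outcome, standardised ones included. That stands too. The change proposed here does not cure it.

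A reader might infer several stronger things that the documents do not support:
- That growth will certainly produce a significant BMI increase. No threshold values, growth rate or SD are given, and at the low end of the assumed range the chance is about 19%.
- That the protocol itself justifies its scaling by the shift of the threshold during growth. It says only that the threshold is specific to age and sex.
- That the FBSFT versus TAU comparison is biased. Growth common to both arms cancels there.
- That the plan will read a BMI time effect as a treatment effect. It does not say so.

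**Conclusion.** The point holds in a limited form. As written, the one-way time analysis includes raw BMI and raw waist in children aged 6–18 without a control group. If the IOTF-25 threshold rises with age, the time effect on raw BMI combines growth and treatment. The direction follows from the protocol's formula plus that one assumption. For BMI it runs against treatment, so it could hide or reverse an apparent long-term benefit but not create one. A joint MANOVA has no sign and could be significant through growth alone. Raw waist is open to the same objection, but its drift was not quantified.

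The size is wholly conditional on the assumed inputs: 0.7–2.8 kg/m² over 24 months, with a significant upward effect in roughly 19% to 99% of trials at 60 children, SD 5 and correlation 0.5. It is smaller for participants near adult age if, as one would expect, the threshold levels off there. Two of the three primary measures and the randomised comparison are largely untouched. The text should be changed, but the trial's main comparison is not threatened.

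**What to change.** In Planned data analysis, restrict the one-way time analysis to BMI SDS or %IOTF-25 for weight, and to waist SDS or waist-to-height ratio for waist. Report raw BMI and raw waist over time descriptively only, and keep raw BMI for the between-arm comparison.

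This takes about one sentence and no new data, because every replacement measure is already listed. The cost is that there is no test over time in the familiar BMI unit. The change removes growth drift from the weight and waist measures only. Other outcomes may still shift with age, and the analysis remains uncontrolled, so it should not be presented as evidence of a treatment effect.

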Dropout is a substantial concern in treatment of both adult and pediatric obesity [11, 29, 30], but only a limited number of studies have examined the predictors for dropout [29, 31, 32]. Studies show mixed results regarding barriers to treatment participation. Some studies have found higher number of barriers in families who end the treatment program prematurely [32, 33], while another found few differences in degree of barriers among treatment completers compared to non-completers [31]. Post-treatment reported barriers in prior studies include high degree of family stressors, parent-adolescent conflict, lack of time and interest, interference with school schedules, disappointment with amount of weight-loss, and treatment taking place too far from home [31, 32, 34]. Further research on predictors for dropout and barriers to treatment participation, both among non-completers and completers, has important implications for clinical practice [30].

Another subject of clinical importance is to identify pre-treatment factors related to poorer treatment response. Together with knowledge about predictors for dropout and barriers to treatment participation, these factors can identify at risk groups and tailor childhood obesity treatment to increase treatment response. Several pre-treatment factors have been associated with weight loss outcomes in previous research on childhood obesity treatment [30, 31, 35–38], including child age, gender, child initial weight status [36, 38], child mental health problems [36, 37], and parents’ degree of motivation [30, 31, 35, 36]. However, there seems to be a lack of studies investigating the influence of family variables and broader social network support as predictors of treatment response.

The aim of this paper is to describe and explain the design and evaluation of the Family-based behavioral treatment of childhood obesity (FABO)−study targeting children and adolescents with obesity and their families. The description of the study protocol follows the checklist of the CONSORT statement for randomized trials [39] (Additional files 1 and 2).

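### The weight-related predictor and barrier regressions take %IOTF-25 as a level with no baseline term, so their coefficients mix starting weight with treatment response

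*Protocol article*

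**What the plan says.** All references are to the protocol article.

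- **Purpose.** Planned data analysis introduces the first set of models thus: "In order to identify factors associated with treatment success and treatment drop out, multiple regression analyses will be conducted". The second set concerns how barriers influence treatment response. Study objectives and hypotheses words the expectations as better weight loss and better or poorer treatment effects, for example for parental weight: "higher BMI category will predict poorer treatment effects and higher dropout rate".
- **Outcome.** For the predictor models: "The dependent variables are %IOTF-25 and drop-out status (yes/no"). For the barrier models: "The dependent variable is %IOTF-25". Neither statement gives a time point, a change score or a baseline adjustment.
- **Definition.** Anthropometrical measures: "The percentage of the IOTF 25 threshold (%IOTF-25) is calculated as 100*(BMI/IOTF 25"). This is a ratio formed from one visit's BMI.
- **Predictors.** First model: "The predictors are: both parents participating in treatment, parental marital status, self-reported parental weight, socio-economic status and social network, psychological comorbidities". Second model: "The predictors are: competing activities/life stressors, relevance of treatment, treatment issues (logistics) and critical events". Neither list has baseline %IOTF-25 or treatment arm.
- **Prior knowledge.** The Background lists pre-treatment factors that earlier research has associated with weight-loss outcome, "including child age, gender, child initial weight status [36, 38"] among them.
- **Size.** Sample size gives 55 persons for testing one added predictor in a model with five in total. It assumes a correlation of 0.5 between measurement points for the group-by-time calculation.

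**The concern.** Treatment success and response describe what happens between baseline and follow-up. A follow-up level reflects both where the child started and what happened afterwards. Admission criteria set a lower limit on severity and no upper limit, so starting levels can differ widely.

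A factor that goes with a heavier start will then tend to predict a heavier follow-up even if it has no bearing on response. This is plausible for parental weight, socio-economic status and psychological comorbidity, three of the hypothesised predictors. Where such a correlation runs in the hypothesised direction, the hypothesis can appear confirmed for the wrong reason. Where a factor helps response but goes with a heavier start, its benefit can be hidden. These results are meant to identify groups at risk of poor response, so either error would mislead later tailoring of treatment.

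**Working it through.** **1. The plan's own figure.** Test of one added predictor among p: λ = f²·N, with 1 and N − p − 1 degrees of freedom. With f² = 0.15, N = 55 and p = 5, λ = 0.15 × 55 = 8.25 on 1 and 49 df. Power is 0.804, so 55 is reproduced. (The article writes f = 0.15. Taken literally, f² = 0.0225 and N = 351. That is a separate matter.)

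**2. What the level coefficient contains.** In standardised form, let a predictor correlate r_b with baseline, let baseline and follow-up correlate ρ, and let the predictor have no effect on follow-up given baseline. Its correlation with the follow-up level is then r_b × ρ, which is not zero unless r_b = 0.

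**3. Closed form, N = 120, two-sided 5% test.** Noncentrality is r√N / √(1 − r²).
- r_b = 0.2, ρ = 0.5: r = 0.10; 0.10 × 10.95 / 0.995 = 1.10; rejection about 19%.
- r_b = 0.3, ρ = 0.5: r = 0.15; 0.15 × 10.95 / 0.989 = 1.66; rejection about 38%.

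**4. Simulation, null predictor, N = 120.** Two independent simulations were run: one with the single predictor (4,000 trials per setting), one with four further null predictors in the model (1,000 per setting). Where two figures are given, they come from the two simulations in that order; the ρ = 0.8 row comes from the second only.

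| ρ | r_b = 0.2, level | r_b = 0.3, level |
|---|---|---|
| 0.5 (plan's value) | 20% / 20% | 37% / 36% |
| 0.8 (assumed) | 42% | 77% |
| 0.9 (assumed) | 51% / 48% | 85% / 85% |

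Baseline-adjusted models rejected in about 4% to 6% of runs. Change-score models, run in the second simulation only, rejected in 3% to 5%. With N = 60 (the size of one arm), the level model rejected in 13% to 28% at r_b = 0.2 and 22% to 55% at r_b = 0.3 over the range of ρ.

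**5. Real effects.** Suppose the predictor truly improves change (standardised effect −0.3), with N = 120.
- r_b = 0.2, ρ = 0.5: power 41% for the level model, against 89% to 91% for the adjusted or change model.
- r_b = 0.2, ρ = 0.8: 6% against 89% to 92%. At ρ = 0.9 the average level coefficient has the wrong sign.
- r_b = 0: no bias, and the type I error is correct. Power is 79% against 91% to 93% at ρ = 0.5, and 48% against 92% at ρ = 0.8.

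**6. Cost of adjusting.** With baseline added (p = 6), power at N = 55 is 0.8036. With baseline and arm (p = 7) it is 0.8032. The required N stays at 55.

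**Assumed, not in the documents:** r_b of 0 to 0.3, ρ above 0.5, the effect of −0.3 and, for the change-score comparison, change unrelated to baseline.

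**The case against.** The best defence is that the article is a condensed text and names only the measurement scale. It does not say that the value enters unadjusted, and it does not rule out a change score or a baseline term. The primary outcome is described in the same shorthand although its analysis uses pre and post values. The stated purpose would fit an adjusted model, and such detail is often left to an analysis plan. This stands in part: the conclusion is about the text as written, and the authors may intend something better. It does not dispose of the point. The article names the outcome, defines it as a single-visit level and lists the predictors, so a later document would have to correct this specification and not merely fill it in.

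The predictor count settles nothing. Five in total matches the five listed items, but there are six if socio-economic status and social network are counted separately.

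Three further objections hold. The bias needs a correlation with baseline that the documents do not give. The reason to expect one covers parental weight, socio-economic status and psychological comorbidity; none is offered for the barrier groups, for both parents taking part or for marital status. And %IOTF-25 is already scaled to age and sex, so those covariates are not shown to be necessary.

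On arm, leaving it out does not confound predictors fixed before randomisation; it costs precision. Experienced barriers are different. FBSFT has 17 weekly clinic sessions, while TAU has monthly local sessions and quarterly clinic visits, so logistic barriers could differ by arm. The article does not say which arms enter these models.

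**Conclusion.** The point holds for the text as written. The weight-related regressions for objectives 2 and 3 do not isolate response, because starting weight enters the outcome and is not adjusted for. For a predictor with no effect on response and an assumed correlation of 0.2 to 0.3 with baseline, the false-positive rate is about 20% to 37% at N = 120 and ρ = 0.5. It rises to roughly 50% to 85% if ρ is 0.9. With no correlation, only power is lost.

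A reader might infer that these regressions would find who started heavier *instead of* who responded, or that all the hypotheses are tilted towards confirmation. The documents do not support that. The coefficient is a mixture, its balance depends on correlations that are not stated, and some predictors may be unrelated to starting weight. Nor does the problem reach the drop-out regression or the randomised FBSFT-TAU comparison. It should be corrected before the predictor and barrier analyses are run, but it does not threaten the trial's main result.

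**What to change.** In both weight-related regressions:

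- name the follow-up time point, since the Outcome measures section lists several;
- use follow-up %IOTF-25 as the outcome, with baseline %IOTF-25 as a covariate;
- add treatment arm wherever both arms are pooled, and say which arms enter.

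Age and sex are optional. An interaction with arm is needed only if a factor is claimed to modify the effect of FBSFT. The drop-out model needs no change on this account.

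The cost is a sentence or two in the analysis section and one or two model degrees of freedom. Baseline %IOTF-25 is already collected, no further families are needed, and adding the baseline term leaves the stated 55 as it is.

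### The predictor and barrier regressions list no child age, sex or initial weight status, all named in the Background as correlates of weight loss, so family-factor and barrier coefficients may partly reflect them

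*Protocol article*

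**What the plan says.** The Planned data analysis section of the protocol article sets out two sets of multiple regressions.

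- **Success and dropout.** The dependent variables are %IOTF-25 and dropout (yes/no). The terms are given as: "The predictors are: both parents participating in treatment, parental marital status, self-reported parental weight, socio-economic status and social network, psychological comorbidities". Counting socio-economic status and social network separately, that is six predictors.
- **Barriers.** The dependent variable is %IOTF-25. The terms are given as: "The predictors are: competing activities/life stressors, relevance of treatment, treatment issues (logistics) and critical events".

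No covariate adjustment is mentioned for either set.

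Three other places bear on this:

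- The Background states: "Several pre-treatment factors have been associated with weight loss outcomes in previous research on childhood obesity treatment". It goes on to name them, "including child age, gender, child initial weight status", followed by child mental health problems and parents' motivation.
- Inclusion criteria: "The sample will consist of 120 children and adolescents (aged 6–18 years) referred to the OOC".
- Anthropometrical measures defines %IOTF-25 as 100 × BMI / IOTF 25, where "IOTF 25 is the BMI that corresponds to the IOTF threshold for overweight for the child’s age and sex".

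**The concern.** The Background identifies child age, sex and initial weight status as correlates of weight outcome, and then says that family variables and wider social support have been too little studied as predictors. The regressions meant to fill that gap contain the family and social variables but none of those three correlates.

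In a sample spanning 12 years of childhood, several listed predictors could plausibly vary with the child's age: whether both parents attend, whether they live together, the social network, psychological symptoms and competing activities. If response also varies with age, an unadjusted coefficient mixes the two. A family factor or barrier with no association of its own could then be reported as a predictor of success. The Background says such results would be used to identify at-risk groups and tailor treatment.

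The issue is sharper for the barrier regression, whose stated purpose is how barriers influence response, than for the predictor regression, which is described as looking for associated factors.

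**Working it through.** **1. The plan's own regression sample size.** The Sample size section gives effect size 0.15, one tested predictor, five predictors in total and N = 55. Alpha 0.05 and power 0.80 are carried over from the preceding sentence there. For the F test of an R² increase, the numerator df is 1, the denominator df is N − p − 1 (p = total predictors) and the noncentrality is λ = f² × N.

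- N = 55, p = 5: df = 49, λ = 0.15 × 55 = 8.25, critical F = 4.04, power 0.804.
- N = 54, p = 5: power 0.796.

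So 55 is reproduced, with 0.15 read as f². The article prints it as f; read literally (f² = 0.0225), the answer would be 351.

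**2. Cost of the extra covariates, holding partial f² at 0.15.**

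| Total predictors | How it arises | Required N | Power at 55 | Power at 60 | Power at 120 |
|---|---|---|---|---|---|
| 5 | as in the Sample size section | 55 | 0.804 | 0.838 | 0.988 |
| 7 | 4 barriers + age, sex, baseline %IOTF-25 | 55 | 0.803 | 0.838 | 0.988 |
| 8 | 5 + the same three (or 6 listed + age, sex) | 55 | 0.803 | 0.837 | 0.988 |
| 9 | 6 listed + the same three | 55 | 0.803 | 0.837 | 0.988 |

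Sample size is therefore no reason to leave them out of the linear models. This calculation does not cover the dropout model, whose outcome is binary.

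**3. How large the misattribution could be.** The article gives no correlation of age with any predictor or with response, so both are assumed. Let r be the correlation of age with a predictor that has no association of its own, and b the correlation of age with response. Without age in the model, the standardised coefficient of that predictor is about r × b. Its t test has noncentrality δ = √N × rb / √(1 − (rb)²).

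Example with r = b = 0.3 and N = 120: rb = 0.09, δ = 10.954 × 0.09 / 0.996 = 0.99, and the two-sided rejection rate at 5% is 16.6%.

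| r / b | rb | δ (N = 120) | False positives, N = 120 | False positives, N = 60 |
|---|---|---|---|---|
| 0.1 / 0.2 | 0.02 | 0.22 | 5.5% | 5.3% |
| 0.2 / 0.2 | 0.04 | 0.44 | 7.2% | 6.1% |
| 0.2 / 0.3 | 0.06 | 0.66 | 10.0% | 7.4% |
| 0.3 / 0.3 | 0.09 | 0.99 | 16.6% | 10.6% |
| 0.4 / 0.4 | 0.16 | 1.78 | 42.1% | 23.5% |

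Simulations at N = 120 agree: 6–7% at 0.2/0.2, about 10% at 0.2/0.3, 15–17% at 0.3/0.3 and 40–43% at 0.4/0.4. The lower ends come from models that also hold five unrelated predictors. With age in the model the rate is 4–6% throughout. If r = 0 there is no inflation, whatever b is.

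These figures are for a continuous outcome and for age alone. Sex, initial weight status and binary dropout were not simulated.

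**The case against.** **The lists may name only the factors under test.** They match the hypotheses in Study objectives and hypotheses almost item for item, and the article never says the models are unadjusted. Covariates for secondary regressions are often left to the analysis plan, which is not shown. This has weight. But both lists are introduced as the predictors of the model, without qualification, and the omitted variables are ones the article itself cites. A later plan that follows the published text inherits the gap.

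**Objective 2 asks for predictors, not independent effects.** A factor that marks risk partly through age can still be a useful marker. That is fair for identifying at-risk groups. It is weaker for the barrier model, and weaker for any claim that family variables add to what is already known.

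**%IOTF-25 is already indexed to age and sex.** This removes the normal age and sex gradient in BMI level, and it stands as a mitigation. It does not remove differences in treatment response by age or sex, and it has no bearing on dropout.

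**Stronger readings a reader might infer.**
- That age effects will be credited to family factors. The article does not establish this: confounding needs age to be related to both predictor and response in this sample, and neither correlation is given. For parental weight and socio-economic status no link with the child's age is evident.
- That age and sex confound the dropout results. The Background ties them to weight loss outcome, not to dropout, so that part is inference.
- That the FBSFT versus TAU comparison also needs adjusting. That does not follow, because randomisation protects it from systematic confounding.

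**Conclusion.** The point stands as a limitation of the secondary regressions. As listed, they omit three correlates of weight outcome that the article names, and nothing in the sample size calculation requires the omission. Family-factor and barrier coefficients may therefore partly reflect the child's age or sex.

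The consequence ranges from negligible (a 5–7% false-positive rate at correlations of 0.2 or weaker) to serious (about 42% at 0.4/0.4), and the article does not allow a choice within that range. The range assumes a linear outcome, N = 120 and age as the only omitted variable. With 60 families analysed the inflation is smaller, reaching about 23% at 0.4/0.4. The primary comparison of FBSFT with TAU is not affected.

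**What to change.** In Planned data analysis, add the following:

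- In the %IOTF-25 predictor and barrier regressions, include baseline child age (continuous), sex and baseline %IOTF-25 as fixed covariates.
- In the dropout regression, include age and sex, stated to be a precaution.
- Report family factors and barriers as associations beyond these covariates.

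The cost is a sentence or two of wording and three degrees of freedom in each %IOTF-25 model (two parameters in the dropout model). No new data are needed, since age, sex and baseline BMI are already required to compute %IOTF-25. The required N for the linear models stays at 55. The cost in the dropout model depends on the number of dropouts, which the article does not project.
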